Neuromuscular training, which usually refers to either proprioceptive drill, strength training, or a combination of both [23, 24], is an effective intervention modality in treating the sensorimotor deficits of individuals with CAI [25, 26]. However, it has not been fully determined as to which neurophysiological mechanism contributes the most to the benefits of neuromuscular training. Based on the existing hypothesis, the mechanism underlying the effect of neuromuscular training on sensorimotor deficits may be related to both spinal (e.g., altered H-reflex) and supraspinal adaptation (e.g., feed-forward reflexive mechanism) [4, 27, 28], yet relevant evidence is lacking for these hypotheses. As one form of neuromuscular training, whole-body vibration (WBV) has been widely studied in different areas such as sports [29], rehabilitation [30], and public health [31]. The possible mechanism of WBV benefits is that it could facilitate reflexive activation at both the spinal and supraspinal level in the central nervous system [32, 33]. To be specific, WBV has been shown to be capable of modulating spinal excitability in a human trial [34], and modulating synaptic plasticity [35, 36] and neurogenesis [37] in the brain of animals. Regarding the effectiveness of WBV for CAI, it has been found that additional benefits could be achieved in sensorimotor deficits (e.g., postural control, strength, and muscle activity) when WBV was added as a supplementary tool [38–40]. Nevertheless, it was still unknown whether the improvements in sensorimotor functions were associated with plastic changes in the brain for people with CAI. Investigation of the relationship between effectiveness of WBV and brain plasticity may provide understanding regarding the pathways through which WBV works on CAI [16].

Therefore, a single-blind randomized controlled trial will be designed to answer the following questions: (a) if WBV can generate sensorimotor benefits for patients with CAI? (b) is there a correlation between changes of sensorimotor functions and alterations of brain plasticity for participants with CAI? In this study, We hypothesize that there will be plastic changes in the brain after the WBV intervention, and these alterations will be correlated with changes in sensorimotor functions.

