### Brain plasticity

In the present study, transcranial magnetic stimulation (TMS) will be used to assess corticomotor alterations including cortical excitability, corticospinal inhibition, and representation of muscles. Single magnetic pulses (max 4 Tesla) will be delivered to the cortical representation of the lower leg muscles by a double-cone coil with TMS equipment (PowerMAG, Mag&More Inc., Germany). All participants will wear an elastic cap and sit on the chair with a relaxed lower limb. A wireless electrode of Delsy’s sEMG system (Trigno, Delsys Inc., Natick, MA, USA) will be placed on the muscle belly of the tibialis anterior and peroneus longus to collect the motor evoked threshold (MEP). The surface of these muscles will be shaved and cleaned with alcohol-impregnated tissues prior to electrode placement. The EMG signal will be collected at a sample rate of 2000 Hz and analyzed using the Matlab software (Matlab 2022a, MathWorks Inc., Natick, USA) with band-pass filters (high-pass of 10 Hz and low-pass of 500 Hz). Prior to the official test, the familiarization procedure will be conducted to reduce any apprehension caused by the magnetic stimuli. The method of identifying a hot spot will be in line with the one reported in a previous study [67]. The double-cone coil will be moved and delivers pulses (70% of magnitude, 5-s interval) to the vertex of the skull. The hot spot will be identified and marked until the maximum peak-to-peak MEPs (50 μV) are found. Subsequently, the stimulation magnitude on the hot spot decreases by 50% until MEP will not be elicited, and then increases by 1%. Rest motor threshold (RMT) will be defined as the stimulation magnitude by which 5 out of 10 pulses generate MEP > 20 μV [18]. Active motor threshold (AMT) will be defined as the least MEP intensity eliciting peak-to-peak MEP amplitude ≥ 100 μV in 5 out of 10 pulses. RMT and AMT will be presented as the percentage of maximum Tesla [68]. Corticospinal inhibition will be represented by the cortical silent period (CSP). According to previous studies, the CSP has been defined as the distance from the end of the MEP to the return of the mean EMG signal plus two times the standard deviation of the baseline EMG signal [69, 70]. The map area and the volume of cortical representation in the peroneus longus and anterior tibialis, which are used to represent an expansion of the cortical representation and the total excitability of cortical representation respectively, will be calculated by referring to the method reported previously [12]. All results in the TMS test will be collected in each group and used for statistical analysis.

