### Statistics analysis

As all outcomes are continuous variables, they will be presented as mean ± standard deviation. The normality of variables will be tested by the Shapiro–Wilk test. All statistical analyses will be carried out using the SPSS software (Version 22.0, IBM Corp., Armonk, NY, USA) and *p* < 0.05 will be considered as a significant difference. Bonferroni adjustment will be performed in post-hoc analysis when statistical significance is found. A 1-way ANOVA analysis will be conducted to compare outcomes among the four groups. Pearson's correlation coefficient will be calculated to evaluate the relationship between alterations in sensorimotor function and plastic changes in the brain. The effect size (Cohen’s d, 95% confidence intervals) will be calculated to evaluate the magnitude of difference among groups. Ranges 0.2–0.49, 0.5–0.79, and > 0.8 are considered as small, medium, and large effect sizes respectively. A 2-way repeated-measure ANOVA analysis will be performed in terms of the different time points (i.e., baseline, post-test, and 2-week follow-up) of the various groups (i.e., WBVBT, BT, WBV, and control group). A correlation analysis will be conducted to determine the relationship between changes in sensorimotor deficits and neural plasticity. To estimate the efficacy and effectiveness of interventions, per‑protocol and intention-to-treat analysis will be conducted respectively if any participants withdraw.

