The stimulation of the motor cortex by TMS is a way to investigate the integrity of the brain in regards to muscle pathways and the functionality of cortical networks [80]. The changes from TMS (e.g., RMT, AMT, and CSP) observed in previous studies have indicated that there may be limitations in signal transmission from corticomotor systems to muscles around the ankle [12, 69, 81]. These alterations can be used to explain the changes in biomechanics [82] and kinematics [83] for individuals with CAI. In the current study, results of TMS assessments will be used to determine if there are associations between the sensorimotor changes caused by WBV intervention and alterations in the corticospinal pathway. fNIRS can be viewed as a non-invasive approach to assess functional activation of the brain through cerebral oxygenation changes evoked by haemodynamics [71]. A previous study using fNIRS to investigate alterations of cortical activation found significant differences in cortical-activation variability among individuals with CAI in comparison to a healthy control group [13], indicating that patients with CAI may have different patterns of cortical activation. In the present research, the changes in functional activations when participants stand in a one-legged stance can show how the cortical sensorimotor region responds to the instability of the ankle joints. In addition, the correlation between brain activation and alteration in sensorimotor function may provide evidence to support the strategy of taking brain activation as the target to achieve functional benefits.

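### The correlation analysis for research question (b) has no group term, named pair or multiplicity rule, so a shared training effect or chance can pass for a brain–function link

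*Protocol article*

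**What the plan says.** The Background of the protocol article poses two research questions. The second is: "is there a correlation between changes of sensorimotor functions and alterations of brain plasticity for participants with CAI". The hypothesis that follows is that the brain will change after the intervention and that "these alterations will be correlated with changes in sensorimotor functions".

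The Statistics analysis section states the matching analysis twice. The first statement is that Pearson's "correlation coefficient will be calculated to evaluate the relationship between alterations in sensorimotor function and plastic changes in the brain". The second is: "A correlation analysis will be conducted to determine the relationship between changes in sensorimotor deficits and neural plasticity". Neither names a pair of variables, a change window (post-test or follow-up) or a group term, and neither says whether the arms are pooled or analysed separately. For all analyses, p < "0.05 will be considered as a significant difference". The only multiplicity rule is: "Bonferroni adjustment will be performed in post-hoc analysis when statistical significance is found".

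Other sections bear on which variables could enter:

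- The text of Outcome measures narrows the primary outcomes to SEBT and oxyhemoglobin activation, but Table 2 lists every brain and sensorimotor measure as primary.
- The Brain plasticity section says: "All results in the TMS test will be collected in each group and used for statistical analysis".
- The Discussion uses both TMS and fNIRS for associations with sensorimotor change. It says the correlation with brain activation "may provide evidence to support the strategy of taking brain activation as the target to achieve functional benefits".

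**The concern.** The trial has four arms, one of them without intervention. If training improves balance and also changes cortical activation, people in the trained arms will tend to be higher on both change scores and controls lower on both. A Pearson coefficient over all participants then differs from zero even if, inside every arm, those whose brain changed most are not those whose balance changed most. The coefficient cannot tell a link between the two changes from two separate effects of the same training. The Discussion's idea of brain activation as a treatment target depends on that distinction.

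Correlating within each arm avoids this problem but leaves very small samples. On either route the number of pairs is open, each is judged at 0.05, and the Bonferroni sentence reads as covering group or time comparisons after a significant ANOVA, not correlations.

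The conclusion of the article describes exploring the role of brain plasticity as the main purpose of the study, so this analysis is central to it.

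**Working it through.** **1. The plan's own figure.** The protocol gives no sample size for the correlation. Its ANOVA figure reproduces with f = 0.35, α = 0.05, 4 groups, 3 measurements and an assumed correlation of 0.5 between measurements (between-factors option):

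λ = f²·N·m / (1 + (m − 1)ρ) = 0.1225 × 64 × 3 / (1 + 2 × 0.5) = 11.76, df 3 and 60, power 0.805.

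So N = 64, and 64 / 0.8 = 80, or 20 per arm (16 after the planned dropout). The calculation covers group differences only.

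**2. Pooled correlation with no within-arm link.** Let both change scores have the same pattern of arm means with group effect f, unit SD within arms, and zero correlation within arms. The pooled population correlation is then f² / (1 + f²).

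- At f = 0.35: 0.1225 / 1.1225 = 0.109.
- Check by Fisher's z at N = 64: atanh(0.109) × √61 ≈ 0.855. P(Z > 1.96 − 0.855) + P(Z < −1.96 − 0.855) ≈ 0.135 + 0.002 ≈ 14%.

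Simulated rates for one pair at two-sided 0.05 (sidedness assumed), N = 64 to 80:

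| Group effect f on both changes | Pooled population r | Plain Pearson | Adjusted for group |
|---|---|---|---|
| 0.25 | 0.059 | 7–8% | 5% |
| 0.35 | 0.109 | 14–16% | 5% |
| 0.50 | 0.200 | 36–44% | 5–6% |
| 0.80 | 0.390 | 93–97% | 5% |

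The result at f = 0.35 does not depend on one pattern of means. With arm means 0, d, d, d, the SD of the means is √(0.75/4)·d = 0.433d, so f = 0.35 is d ≈ 0.8. A simulation with that pattern gives 14% at N = 64.

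**3. Correlation within arms.** The correlation detectable with 80% power is r = tanh(2.80 / √(n − 3)):

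- n = 16: tanh(2.80 / √13) = 0.65
- n = 20: tanh(2.80 / √17) = 0.59
- pooled, n = 64: tanh(2.80 / √61) = 0.34
- pooled and adjusted for group (three further degrees of freedom): tanh(2.80 / √58) = 0.35

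**4. Multiplicity.** The variable counts are read from the sections on sensorimotor deficits and brain plasticity:

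- Sensorimotor: 8 SEBT directions + TIBT + 4 strength directions + AMEDA + AIDAL + side-hop = 16.
- fNIRS: 3 regions × 2 stance conditions (eyes open, eyes closed) = 6.
- TMS: RMT, AMT, CSP, map area and map volume = 5, or 10 if each is taken for both muscles (an assumption).

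For k independent tests the chance of at least one false positive is 1 − 0.95^k. The measures within a domain are surely correlated and the protocol gives no values, so the simulation uses a common within-domain r from 0 to 0.9, no link between domains, and one change window:

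| Set tested | Pairs | r = 0 | r = 0.5 | r = 0.7 | r = 0.9 |
|---|---|---|---|---|---|
| One SEBT score × 6 fNIRS | 6 | 26–27% | 20–21% | 16–17% | 11% |
| 8 SEBT × 6 fNIRS | 48 | 91–92% | 73% | 50–52% | 24% |
| 16 sensorimotor × 16 brain | 256 | >99% | 99% | 84–85% | 36–37% |

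Testing change to follow-up as well would double the pairs. These rates leave out the arm effect in step 2, which would come on top if arms were pooled.

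**The case against.** The strongest reply is that much of this is detail which a condensed article may leave to a fuller plan: the pairs, the covariates and the multiplicity rule for associations. The text nowhere says that every pair will be tested or that arms will be pooled, and the Brain plasticity section speaks of TMS results collected in each group. A reader might infer that all sensorimotor changes will be correlated with all brain changes, making a significant link near certain even if none exists. The protocol does not support that. The 256-pair grid is a count from the measurement sections, not a stated plan, and the text of Outcome measures points to SEBT and oxyhemoglobin. Near-certainty also fails for small sets or highly correlated measures. All of that stands.

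It can also be said that the question is worded only as a correlation among participants with CAI, that the Discussion is cautious, and that the higher rates in step 2 need effects above the planning value. This stands in part. A pooled coefficient is a valid description of the whole sample, and f = 0.35 was set for group differences in a repeated-measures ANOVA, so carrying it over to both change scores is an assumption.

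The objection does not remove the point. The method is named, not left open: a plain Pearson coefficient at 0.05, which contains no group term. Reading it as within-arm avoids the arm effect only by giving up power for all but strong correlations. The proposed use of the result, brain activation as a target for functional benefit, needs more than two measures that both respond to training.

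**Conclusion.** The concern holds in a conditional form. The stated method for question (b) does not separate a link between brain and function from a shared effect of training, and nothing in the section limits or adjusts the number of correlations.

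- If arms are pooled, a single pair has a false-positive rate of about 14–16% at f = 0.35, roughly three times nominal, against about 5% with group adjustment. False positive here means significance with no association within arms. The figure assumes that treatment shifts both measures with the same pattern of arm means.
- If arms are analysed separately, correlations below about 0.59–0.65 are likely to be missed, against about 0.34 pooled.
- Multiplicity raises the risk by an amount the protocol does not fix: about 11–27%, 24–92%, or 37% to over 99% for 6, 48 or 256 pairs, under assumed within-domain correlations of 0 to 0.9.

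The change should be made. It does not call the ANOVA or its sample size into question.

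**What to change.** Replace the plain Pearson analysis with a partial correlation, or a regression slope, adjusted for allocated group and pooled over the four arms, reported with a 95% CI.

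Name one confirmatory pair and one window from the primary outcomes in the text of Outcome measures: baseline-to-post change in one defined SEBT score with baseline-to-post change in oxyhemoglobin in one named region and stance condition. Both must first be defined, because the protocol lists eight SEBT directions without a composite, and three regions and two stance conditions without a primary one.

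Label every other pair and window exploratory, with false-discovery-rate control, and state the conclusion as association.

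The cost is wording and three degrees of freedom for group, which moves the detectable correlation at N = 64 from about 0.34 to 0.35. No new data are needed. The real price is that TMS and the remaining sensorimotor measures can no longer support a confirmatory claim on question (b).

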**Methods:**

The present study is a single-blind randomized controlled trial. A total of 80 participants with CAI recruited from the university and local communities will be divided into 4 groups: whole-body vibration and balance training (WBVBT), balance training (BT), whole-body vibration (WBV), and control group. Participants will be given the WBV intervention (25-38 Hz, 1.3-2 mm, 3-time per week, 6-week) supervised by a professional therapist. Primary outcome measures are sensorimotor function including strength, balance, proprioception and functional performance. Brain plasticity will be evaluated by corticomotor excitability, inhibition, and representation of muscles, as measured by transcranial magnetic stimulation. Activation of brain areas will be assessed through functional near-infrared spectroscopy. Secondary outcome measures are self-reported functional outcomes involving the Cumberland Ankle Instability Tool and the Foot and Ankle Ability Measure. All tests will be conducted before and after the WBV intervention, and at 2-week follow-up. Per‑protocol and intention-to-treat analysis will be applied if any participants withdraw.

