### Sample size

The needed sample size is calculated using the G-power software (version 3.1.9). The effect size is determined based on the value (0.35) previously reported in a study investigating cortical adaptations after balance training [40, 56]. Other parameters in the software of G-power are α error (0.05), power (0.8), number of groups (4), and number of measurements (3) [74]. Based on the above parameters, the total sample size given by the software is 64. Considering a 20% dropout rate, a total of 80 participants will be included, with 20 in each group.

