Some limitations should be mentioned for the present study. First, compared to participants recruited at a university, patients from the community may have lower compliance because of their holiday, employment or family routines. Second, although participants will be requested to refrain from involvement in specific rehabilitation programs during the experiment, they will not be limited in regard to participation in regular exercises, which may be a factor influencing final outcomes. Third, despite the break provided between each of the tests, the results for brain plasticity and sensorimotor deficits may be interactively influenced, since these two measures are potentially associated [84]. Fourth, prognostic factors such as demographic features (e.g., age, sex), severity of lateral ankle sprain, anatomic configuration, functional performance, and initial treatment could potentially impact on the efficacy or mechanism of WBV, but this study may not be able to explain them clearly [85].

In conclusion, the main purpose of the current study is to explore the role of brain plasticity in the effects of WBV on sensorimotor deficits for individuals with CAI. The findings of this study will provide evidence for treating sensorimotor deficits from the perspective of brain plasticity. In addition, the results may also guide clinical practice when incorporating WBV into rehabilitation programs.

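### Intention-to-treat depends on withdrawal, yet the named repeated-measures ANOVA cannot by itself keep a participant who misses a visit

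*Protocol article*

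**What the plan says.** The Statistics analysis section closes by saying that per-protocol and "intention-to-treat analysis will be conducted respectively if any participants withdraw". It links the two analyses to efficacy and effectiveness in turn. The Methods paragraph of the abstract has the same condition: "intention-to-treat analysis will be applied if any participants withdraw". Neither place names one of the two as primary.

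The longitudinal method is given in the same section: "A 2-way repeated-measure ANOVA analysis will be performed in terms of the different time points", these being "baseline, post-test, and 2-week follow-up", across the four groups. A second comparison stands beside it: "A 1-way ANOVA analysis will be conducted to compare outcomes among the four groups". On software, "All statistical analyses will be carried out using the SPSS software" (version 22.0).

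The Sample size section expects loss: "Considering a 20% dropout rate, a total of 80 participants will be included", up from a calculated 64. Among the limitations, the Discussion adds that "patients from the community may have lower compliance because of their holiday, employment or family routines".

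**The concern.** Intention-to-treat is brought in when someone withdraws. Withdrawal usually means a missing post-test value, a missing follow-up value, or both. The classical repeated-measures ANOVA uses only participants with a value at every time point. The event that triggers the intention-to-treat analysis is therefore the event that takes the participant out of the model named to carry it.

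At stake is the protection that randomisation gives the four-arm comparison. Loss could plausibly be uneven. Three arms train three days a week for six weeks while the control group has no intervention. Two of the four arms receive vibration, for which the safety section lists headache, dizziness and fatigue. Participants are not blinded. There is also a loss of information: someone assessed at baseline and after the intervention who misses only the two-week follow-up loses an observed post-test value as well.

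The trigger also covers only withdrawal. A participant who attends poorly but does not withdraw sets off neither analysis, although the Discussion expects lower compliance in some participants.

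**Working it through.** **1. The plan's own figure.** Inputs from the Sample size section: effect size 0.35 (taken as Cohen's f), alpha 0.05, power 0.80, 4 groups, 3 measurements. Two inputs are assumed because the article does not state them: the test is the between-groups factor of a repeated-measures ANOVA, and the correlation between visits is 0.5.

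- Noncentrality = N × f² × m / (1 + (m − 1) × rho) = 64 × 0.1225 × 3 / (1 + 2 × 0.5) = 23.52 / 2 = 11.76, with 3 and 60 degrees of freedom.
- Power = 0.8045, so 64 is reproduced.
- Dropout: 64 / (1 − 0.20) = 80, as stated.

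The calculation thus already treats dropouts as lost and rests on 64 complete cases.

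**2. Who leaves the analysis.** 0.20 × 80 = 16 randomised participants, leaving 64 (16 of 20 per group if loss is even). This reads the 20% as loss of at least one visit over the whole trial. The article does not split it between missed post-test and missed follow-up. Sixteen is an upper figure, because a person who stops training but attends all three assessments stays in.

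**3. Power is not the issue.** On the same assumptions, power is 0.80 with 64 complete cases and 0.90 (0.8952) if all 80 were fully observed. A model using partial data would lie between. The question is validity.

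**4. When bias arises.** An illustrative two-arm simulation assumed no true effect, correlation 0.5 between visits, and follow-up missing more often in people with lower scores. The all-data estimate predicts follow-up from baseline and post-test, as a stand-in for a likelihood-based mixed model. Entries are the false difference in SD, the arm with more loss minus the arm with less.

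| What drives loss | Loss in the two arms | Completers, post-test | Completers, follow-up | All observed data, follow-up |
|---|---|---|---|---|
| Low post-test score (observed) | 20% / 20% | about 0 | about 0 | about 0 |
| Low post-test score (observed) | 10% / 30% | 0.21 | 0.11 | about 0 |
| Low follow-up score (unseen) | 20% / 20% | about 0 | about 0 | about 0 |
| Low follow-up score (unseen) | 10% / 30% | 0.11 | 0.22 | 0.16 |

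The loss rates and mechanisms are assumptions; none comes from the article. The table shows three things. Equal loss by the same mechanism does no harm to the contrast. Unequal loss tied to observed scores biases the completer analysis, and using all the data repairs it. Unequal loss tied to unseen scores leaves bias in both.

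**The case against.** The strongest reply is that the article nowhere says incomplete participants are dropped. Listwise deletion is a property of the named method. Imputation before the ANOVA would fit the text and may stand in an analysis plan that is not shown. Naming two analyses for two purposes also suggests that two different analysis sets are meant. This stands as a limit: the point is the mismatch between the published method and the intention-to-treat label, not the absence of an imputation rule.

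Three further replies also hold. The one-way ANOVA, if run visit by visit, would keep each person at the visits attended. The trigger wording alone does little harm, since with no withdrawals all 80 are available anyway. And a mixed model does not remove bias from loss that depends on unseen values; a participant with only a baseline value adds almost nothing to the post-baseline contrast.

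A reader might infer more: that both analyses compare adherent completers in the active arms with nearly all controls, and so favour the interventions. The document does not support that. Poor attenders who come to every assessment remain in the intention-to-treat run. Controls can withdraw too, and the dropout allowance gives all four groups 20. Per-protocol is not defined, so whom it would remove is not known.

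A reader might also put a figure on the bias by multiplying the dropout share by an assumed shortfall in response, for example 0.20 × 0.5 = 0.10 SD. That requires dropouts in the control group to show no such shortfall, which nothing in the article establishes.

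**Conclusion.** The point holds as a mismatch between label and method. As published, intention-to-treat is conditional, its rank against per-protocol is not stated, and the longitudinal model named for it does not itself keep anyone with a missing visit. Unless values are imputed, up to 16 of 80 randomised participants would leave that analysis at the planned dropout, and the intention-to-treat run would become an assessment-completer analysis.

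The resulting bias has no fixed size or direction. It depends on whether loss differs between arms and on how loss relates to outcome. The simulated 0.11 to 0.22 SD belongs to the assumed 10% / 30% split and is not a forecast. The conclusion rests on the classical form of the repeated-measures ANOVA and on withdrawal leading to missed assessments.

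**What to change.** In Statistics analysis, state that the primary analysis is intention-to-treat in all cases: every randomised participant, by allocated arm, in a linear mixed model for repeated measures that uses every available visit. Multiple imputation before the planned ANOVA is an acceptable alternative. Name per-protocol as secondary. Remove the condition on withdrawal there and in the abstract.

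State also that participants who stop training are still invited to the post-intervention and follow-up assessments already scheduled. This matters as much as the choice of model, because no model recovers outcomes that were never observed. Add a sensitivity analysis for data missing not at random.

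The cost is a change of wording, slightly more analysis work, and some effort to bring non-completers back for assessment. The sample size of 80 stays.
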